### Data collection

The study data collected at each time point are summarised in table 1. All participating units contribute data to the Intensive Care National Audit and Research Centre (ICNARC) case mix programme. Data collected routinely by units as part of this national audit will be used to provide demographic, diagnostic and severity of illness data for participants. These data will include: age; gender; admission diagnoses; Acute Physiology and Chronic Health Evaluation (APACHE) II severity of illness score; number of organ failures; admission and discharge location; length of stay (in Critical Care and in hospital); status on hospital discharge; and ultimate discharge location. An estimate of each participant's premorbid functional ability (Katz's ADL Index) will be made by interview with their next of kin. For each day a participant remains in Critical Care, we will record the type and total dose of sedatives and the total calorie intake received as enteral or parenteral nutrition. Data related to each physiotherapy session will be collected by the physiotherapist allocated to that session, under the supervision of the research physiotherapist. We will assess participants at discharge from Critical Care against the Modified Rivermead Mobility Index. At hospital discharge, 3 and 6 months after study enrolment, patients will be invited to attend a follow-up appointment where the study assessments will take place. Where feasible, appointments will coincide with routine clinical follow-up, to enhance the likelihood of good compliance. Participants who do not attend their appointment will be followed up by telephone.

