## Analysis

### Statistical analysis

The PCS component of the SF-36 at 6 months following recruitment is the primary end point of the study. In order to test the primary hypothesis of no difference between the intervention and control groups, the principal analysis will examine the difference between the groups on this measure using Analysis of Covariance (ANCOVA) in order to adjust for the effects of covariates in the analysis. The normality of the outcome variable will be assessed and, if necessary, transformations considered although ANCOVA are robust to deviations from this distribution. The covariates to be considered will include stratification variables (unit, admission type and preadmission activity level) in addition to demographic variables such as age and gender. More basic illustrative analyses using the t test or non-parametric alternatives may also be undertaken while, in addition, summary statistics will be calculated.

A broadly similar approach will be used to analyse the secondary outcome measures (the MCS component of the SF-36, the 6 min walk test, FIM, grip strength, quadriceps strength and body mass index (BMI)) at both 3 and 6 months post-study entry, in addition to at hospital discharge. Additionally, the 3-month and hospital discharge data on the PCS component of the SF-36 will be analysed in this fashion, along with the FIM, grip strength and BMI outcomes at Critical Care discharge. Repeated measures methods (again based on analysis of variance) will be employed in order to examine these outcome measures longitudinally across collected time points. Standard survival data methods, such as Kaplan-Meier and the log rank test, will be used to compare survival between the groups at 3 and 6 months. We will also compare durations of Critical Care and hospital stay, in addition to the delirium and ventilator-free days measures.

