There are no planned interim analyses or stopping rules. An allowance for loss to follow-up has been included in the sample size calculation; data with missing observations due to loss to follow-up, as opposed to mortality, will be examined to determine both the extent of missing data and whether data are missing at random or are informative. If data are missing to a sufficient extent, the use of appropriate imputation techniques will be considered to allow for this in the analysis. All analyses will initially be performed on an intention-to-treat basis, although it may be useful to consider additional per-protocol analyses. We may base an analysis on groups defined by a dichotomisation (into long or short) length of stay in Critical Care, in addition to considering other subgroup analyses. A statistical analysis plan will be written and agreed by the Trial Oversight Committee (TOC) before analysis of the study data.

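### The planned ANOVA-based longitudinal analyses conventionally keep only complete series, and the plan to determine from the data whether they are missing at random cannot be carried out

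*Protocol article*

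**What the plan says.** All in the Protocol article.

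- **Primary analysis** (Statistical analysis): ANCOVA of the SF-36 PCS at 6 months, a single time point.
- **Visit-specific analyses** (same section): secondary outcomes, and PCS at the earlier times, are also compared separately at hospital discharge, 3 months and 6 months. FIM, grip strength and BMI are compared at Critical Care discharge as well.
- **Longitudinal analyses** (same section): "Repeated measures methods (again based on analysis of variance) will be employed in order to examine these outcome measures longitudinally across collected time points".
- **Missing data** (same section): the rule covers "data with missing observations due to loss to follow-up, as opposed to mortality". These data "will be examined to determine both the extent of missing data and whether data are missing at random or are informative". The next sentence reads: "If data are missing to a sufficient extent, the use of appropriate imputation techniques will be considered to allow for this in the analysis". No threshold is given. An analysis plan is to be agreed before the data are analysed.
- **Data collection**: "Participants who do not attend their appointment will be followed up by telephone". The secondary outcomes section allows the FIM and other questionnaires to be done by telephone at 3 and 6 months.
- **Table 1**: SF-36 and the walk test are scheduled at hospital discharge, 3 months and 6 months. SF-36 is not scheduled at randomisation.

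**The concern.** Three stated choices fit this population poorly.

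1. Classical repeated-measures ANOVA needs a full series, so one missed visit removes the participant and the visits that were made. The trial's objective is the rate as well as the magnitude of recovery, and this is the named analysis of outcomes across time. Walk and dynamometer tests cannot be done by telephone, so incomplete series are to be expected for them.
2. Hospital discharge falls at a different time for each participant, and length of hospital stay is itself compared between arms. If treatment alters stay, a comparison at discharge mixes the effect of treatment with time since randomisation.
3. A check that claims to tell missing at random from informative loss gives false assurance whichever way it comes out. An imputation trigger without a threshold leaves open how the 6-month PCS estimate treats survivors who were lost.

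**Working it through.** **Step 1. The plan's own figures.** Inputs from Sample size: difference 5, SD 11, power 80%, significance level 0.05 (taken as two-sided), mortality about 40%, other loss a further 10%, total 308.
- n per group = 2 × (1.96 + 0.84)² × 11² / 5² ≈ 76 by normal approximation. The t-based solution is 76.9, that is 77, as stated.
- 154 / (1 − 0.40 − 0.10) = 308, as stated.

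Both figures reproduce, and neither is in dispute here.

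**Step 2. Loss among survivors.**
- Survivors at 6 months: 0.60 × 308 = 184.8.
- Other loss: 0.10 × 308 = 30.8.
- Loss as a share of survivors: 30.8 / 184.8 = 16.7%. This leaves 154 with a 6-month value.

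**Step 3. Complete three-visit series among survivors.** The documents give no loss rate for the earlier visits, so these are assumptions.

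| Assumption | Share complete | Number of 184.8 |
|---|---|---|
| 16.7% lost at each visit, independently | 0.833³ = 58% | 107 |
| 16.7% lost at 6 months, 10% at each earlier visit, independently | 0.833 × 0.9² = 67.5% | 125 |
| 10% lost at each visit, independently | 0.9³ = 73% | 135 |
| 16.7% lost, the same people throughout | 154 / 184.8 = 83% | 154 |

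The plan's own 6-month allowance caps the share at 83%.

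**Step 4. Can the data show the mechanism?** Comparing earlier scores of those who attend and those who do not can reject missing completely at random. Whether loss is at random or informative turns on whether, given what was observed, it still depends on the unseen value. That value is by definition not in the data, so models of both kinds can fit the observed records equally well.

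**Step 5. Illustration by simulation.** All inputs are assumptions except the SD and target difference: true difference 5 at each of three visits, SD 11, within-person correlation 0.6. Dropout is permanent. In the control arm it depends on score; in the intervention arm it does not.

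| Control-arm dropout depends on | Lost by 6 months (control / intervention) | Completers only | All observed visits |
|---|---|---|---|
| Earlier observed scores only | 19% / 13% | 3.7 | 5.0 |
| Earlier and unseen scores | 26% / 13% | 1.9 | 3.8 |

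Using all visits removes the bias when the missing-at-random assumption is true and only part of it when it is not. This is why a sensitivity analysis is needed as well as a better model.

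**Step 6. Reach into the primary analysis.** The 6-month ANCOVA does not require earlier visits, so Step 3 does not reduce it. If imputation is not done, its complete-case bias for survivors is p₁d₁ − p₀d₀, where p is the share lost in an arm and d is observed minus lost mean PCS. With p = 0.167 in both arms and d₀ = 0, a d₁ of 3, 5 or 8 points (assumed) gives 0.50, 0.83 or 1.33. With equal p and equal d it gives zero.

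**The case against.** The strongest reply has five parts.

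- **The wording names a family of methods, not a procedure.** No complete-case rule is written, and imputation, if done, could avoid listwise deletion. This stands: dropping incomplete series is the usual consequence of the method named, not something the article states.
- **Imputation does not wait on the mechanism check.** A reader might infer that the plan imputes only after finding data missing at random or informative. The text does not support that. The written condition is extent, which can be applied whatever the mechanism, and the check is a separate aim. What remains is that the check itself is unachievable and the extent is undefined.
- **The detail belongs in the analysis plan.** This is fair for imputation variables, covariance structure and thresholds. It does not rescue two things the article does state: the ANOVA basis, and the aim of determining the mechanism from the data.
- **The reach is limited.** The longitudinal analyses are secondary, each visit is also analysed on its own, and PCS can be collected by telephone. All of this stands. The telephone limitation applies to the physical tests only.
- **The loss figures are pessimistic.** Misses tend to cluster in the same people, which moves the share complete towards 83%. This is why a range is shown.

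A reader might also infer that discharge assessments can fall after month 3. The article does not say so, and Table 1 lists hospital discharge before the 3-month visit. The point needs only that discharge has no fixed time.

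**Conclusion.** The point holds for the secondary longitudinal analyses and for the wording of the missing-data rule. Complete series for about 58% to 83% of survivors is the plausible range, given 10% to 16.7% loss per visit and the cap set by the plan's 6-month allowance. The spread comes from how misses cluster, which the documents do not tell us.

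It does not show that the primary result is biased. The 0.5 to 1.3 point figure (10% to 27% of the 5-point target) needs lost survivors to differ from observed ones in one arm only, and the documents give no source for that. The simulation likewise assumes selective dropout in one arm. Both show what could happen, not what is expected.

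Most of the missing 6-month values will be deaths (about 40%, against 10% for other loss). The article rightly sets these apart, and neither a mixed model nor imputation under missing at random resolves them.

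**What to change.** **Longitudinal analyses.** Replace repeated-measures ANOVA with a likelihood-based mixed model with treatment-by-visit terms, unstructured covariance and the stratification factors, fitted at 3 and 6 months. Use all available records from participants alive at each time. State how deaths between 3 and 6 months are handled, so that the model does not implicitly predict 6-month scores for people who have died. Describe the results as estimates among survivors and report them beside the survival comparison. Analyse discharge values separately.

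**6-month PCS.** Delete the aim of determining whether data are missing at random. State missing at random as an assumption, and prespecify multiple imputation for survivors lost to follow-up. The imputation model should use discharge and 3-month PCS, the stratification factors and baseline variables such as age and APACHE II. Add delta-adjusted sensitivity analyses, with the shift varied separately by arm.

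**Cost.** Wording in the analysis plan, modest programming, and reliance on an openly stated assumption. No new data are needed. The trial is described as still in follow-up and the analysis plan as yet to be written, so there is time to make the change.

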**Methods and analysis:**

308 adult patients who have received more than 48 h of non-invasive or invasive ventilation in Critical Care will be recruited to a patient-randomised, parallel group, controlled trial, comparing two intensities of physiotherapy. Participants will be randomised to receive either standard or intensive physiotherapy for the duration of their Critical Care admission. Outcomes will be recorded on Critical Care discharge, at 3 and 6 months following initial recruitment to the study. The primary outcome measure is physical health at 6 months, as measured by the SF-36 Physical Component Summary. Secondary outcomes include assessment of mental health, activities of daily living, delirium and ventilator-free days. We will also include a health economic analysis.

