**Figure 4 BMJOPEN2015008035F4:**
[figure not shown]
Strengthening programme algorithm.

The control group will receive the standard intensity of physiotherapy which is normally given on participating units. This will consist of no more than 30 min of active exercise comprising: functional retraining (figure 3) and, if time permits, an individually tailored exercise programme, based on a muscle-strengthening algorithm (figure 4). Physiotherapy will occur from Monday to Friday as there is no physiotherapy service available routinely at weekends.

The intervention group will receive an augmented programme with a target delivery of 90 min of active exercise per day, again from Monday to Friday. The physiotherapy sessions will consist of functional retraining (figure 3) and an individually tailored exercise programme, based on a muscle-strengthening algorithm (figure 4). The delivery of this treatment will be divided into one or more sessions depending on: the individual participant's tolerance of the programme; the need for other medical and nursing interventions; and the progression of the participant's recovery.

During the physiotherapy sessions, participants will be monitored closely, and if any of the following occur, the session will be stopped: MAP <60 mm Hg; heart rate <40 or >130 bpm; oxygen saturation <88% (or, if known respiratory disease, a 10% decrease from normal oxygen saturation); marked ventilator asynchrony; participant distress; new arrhythmias; myocardial ischaemia; concern for airway integrity; endotracheal tube removal; fall to knees; or any other significant event where the participant is unable to continue rehabilitation.

Apart from the difference in the intensity of physiotherapy, both groups will have the usual rehabilitation pathway in participating units.

Following discharge from Critical Care, both groups will receive the same, standard intensity of ward-based physiotherapy, and continue with their rehabilitation pathway. In line with NICE guidance, participants will receive an exercise diary to continue independently on discharge from hospital. Any patient readmitted to Critical Care will receive standard physiotherapy care during the second and any subsequent readmissions. All readmissions will be recorded.

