### Randomisation

Participants will be randomised in a 1:1 ratio, using permuted random block allocation, to either intervention or control group. The randomisation process will be administered centrally by Newcastle Clinical Trials Unit via a secure web-based system. Randomisation will be stratified by admitting Critical Care Unit, type of admission (surgical or medical) and the participant's prehospitalisation activity level. We will use Katz's ADL Index^22^ to stratify participants into either ‘low’ activity (score of 0–3) or ‘high’ activity (score of 4–6).

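### The one subgroup the plan names, long or short Critical Care stay, is defined after randomisation; if treatment changes stay, contrasts within it are open to selection bias

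*Protocol article*

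**What the plan says.** In the protocol article, Statistical analysis, the text on subgroups reads: "We may base an analysis on groups defined by a dichotomisation (into long or short) length of stay in Critical Care". Other subgroup analyses are mentioned in the same sentence but none is named, and no cut-off between long and short is given.

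Three other places bear on this choice of variable:

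- Statistical analysis, secondary outcomes: "We will also compare durations of Critical Care and hospital stay". Critical Care stay is therefore also an outcome.
- Abstract, Methods and analysis: "Participants will be randomised to receive either standard or intensive physiotherapy for the duration of their Critical Care admission". Stay therefore sets the time on allocated treatment. Under Study intervention, both arms receive the same ward physiotherapy afterwards.
- Randomisation: "Randomisation will be stratified by admitting Critical Care Unit, type of admission (surgical or medical) and the participant's prehospitalisation activity level". Stay is not, and could not be, among the stratification factors.

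The article defers detail to a statistical analysis plan that the Trial Oversight Committee is to agree before the data are analysed.

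**The concern.** A subgroup analysis keeps the protection of randomisation when the subgroup is fixed before treatment starts. Critical Care stay is not. It is observed at the end of the treatment period, and the plan itself allows that the arms may differ on it.

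Suppose intensive physiotherapy shortens stay. Some patients who would have been long stayers under standard care become short stayers under the intervention. They are sicker than the typical short stayer, so they lower the average prognosis of the intervention arm's short group. The patients left in its long group are the sickest, so the average prognosis falls there too. Comparing arms within either group then mixes any treatment effect with a difference in case mix that the treatment produced. This is selection bias from conditioning on a post-randomisation variable.

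At stake is the reading of the one named subgroup. A contrast in long or short stayers would look like a randomised comparison without being one. Because treatment lasts as long as the stay, the split also separates patients by length of exposure, which makes the result harder still to interpret. The fault lies in the kind of variable proposed, so it is not a detail that the analysis plan can settle by choosing a cut-off.

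**Working it through.** **The plan's own figures first.** Sample size gives a 5-point difference, SD 11, power 80% and significance level 0.05 (taken as two-sided). A two-sample t-test needs 76.95, so 77 per arm, as stated. Total 154 / (1 - 0.40 - 0.10) = 308, as stated. These figures are not in dispute; the SD of 11 and the 77 per arm are used below.

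**Assumed inputs, none in the documents.**

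- No true effect of treatment on PCS.
- Treatment multiplies stay by 0.8 or 0.7 (shortening of 20% or 30%).
- SD of log stay 0.8 within each arm.
- Severity correlates 0.3 to 0.4 with PCS (sicker, lower PCS) and 0.5 to 0.6 with log stay (sicker, longer stay), in absolute size. It is the only link between the two, so PCS and log stay correlate at r = 0.3 × 0.5 = 0.15 up to 0.4 × 0.6 = 0.24.
- Normal distributions, and a split at the pooled median stay.

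**Formula.** Let τ be the shift in log stay in SD units and a = τ/2. Measured on its own arm's standardised scale, the long group is everyone above +a in the intervention arm and above -a in the control arm. With φ and Φ the standard normal density and distribution function, the mean standardised log stay in the long group is φ(a)/(1 - Φ(a)) under intervention and φ(a)/Φ(a) under control. The false PCS difference is

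bias = -11 × r × [φ(a)/(1 - Φ(a)) - φ(a)/Φ(a)],

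and by symmetry it is the same in the short group.

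**Low end (20% shorter, r = 0.15).** τ = -ln(0.8)/0.8 = 0.279, a = 0.1395, φ(a) = 0.395, Φ(a) = 0.555. The bracket is 0.889 - 0.711 = 0.177 (from unrounded values), so the bias is -11 × 0.15 × 0.177 = -0.29 points. The short group holds 56% of the intervention arm and 44% of the control arm.

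**High end (30% shorter, r = 0.24).** τ = -ln(0.7)/0.8 = 0.446, a = 0.223, φ(a) = 0.389, Φ(a) = 0.588. The bracket is 0.945 - 0.662 = 0.283, so the bias is -11 × 0.24 × 0.283 = -0.75 points. The short group holds 59% of the intervention arm and 41% of the control arm.

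So the bias is about -0.3 to -0.8 points in both groups. Simulation with 2 million patients per scenario agrees (-0.27 to -0.75), and the unstratified contrast stays near zero.

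**Wider range.** Simulation with 4 million patients per scenario, with τ and r set directly:

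| τ (SD of log stay) | r | Bias, long / short | All patients |
|---|---|---|---|
| 0 | 0.16 to 0.49 | within 0.03 of zero | about 0 |
| 0.2 | 0.16 | -0.25 / -0.21 | about 0 |
| 0.3 | 0.30 | -0.63 / -0.64 | about 0 |
| 0.5 | 0.49 | -1.73 / -1.73 | about 0 |

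The formula gives -0.22, -0.64 and -1.71 for the last three rows.

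**Against the noise.** Half of 77 is about 38 per arm in each group. The standard error of a difference is 11 × √(2/38) = 2.5 points. A bias of 0.3 to 0.8 is 0.12 to 0.32 standard errors and moves a two-sided 5% error rate to about 5.2-6.2%; a bias of 1.7 moves it to about 10%. Power for a true 5-point difference in a half-size group is about 51% by the normal approximation.

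**The case against.** The best defence is that little hangs on this analysis. It is optional, it comes after an intention-to-treat primary analysis that it cannot alter, and the bias is small against a standard error of 2.5 points. It also needs treatment to move stay: the 20-30% shortening is assumed, and with no shift the bias disappears. All of that stands, and it limits the severity. It does not make the variable a sound choice, because the plan itself treats stay as something the arms may differ on and baseline alternatives are at hand.

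Three stronger readings are tempting, and the documents do not support them.

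- **That the split would manufacture a benefit in long stayers.** In the model above the bias runs against the intervention in both groups and is nearly equal in each. It would tend to hide a benefit, and it would not create a spurious contrast between long and short stayers. Nor does death in Critical Care add much: those patients have no 6-month PCS and cannot enter that contrast.
- **That the within-group contrasts are certainly biased.** The bias is conditional on treatment changing stay, which the documents do not establish.
- **That the plan also proposes a per-protocol set built on tolerance.** The text says only that "it may be useful to consider additional per-protocol analyses" and defines no set, which is ordinary content for the analysis plan. Under Study intervention, tolerance is one of three factors governing how the daily exercise is "divided into one or more sessions depending on: the individual participant's tolerance of the programme". It is not an analysis-set criterion, so no size can be put on a per-protocol bias from this document.

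**Conclusion.** The point holds for the length-of-stay subgroup alone. Stay is observed after randomisation, is compared between arms as an outcome and determines time on allocated treatment, so contrasts within long and short stayers are not protected by randomisation if treatment changes stay. With stay shortened by 20-30% and the assumed correlations, the bias is roughly 6% to 16% of the 5-point target (0.3/5 to 0.8/5), against the intervention. These sizes rest wholly on inputs the documents do not give, and stronger assumed inputs reach -1.7 points. The primary intention-to-treat ANCOVA is unaffected. Severity: should-fix. It is a poor choice of subgroup variable in an optional analysis, and easily put right before the analysis plan is agreed.

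**What to change.** Drop long or short Critical Care stay as a treatment-effect subgroup. If the investigators wish to keep it, report it as descriptive only, with a statement that its groups are formed after randomisation.

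In its place, name baseline modifiers that the trial already collects: the Katz activity stratum, admission type (both stratification factors) and APACHE II. Examine each by adding a treatment-by-baseline interaction to the ANCOVA for 6-month PCS.

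The cost is about one sentence in the analysis plan and no new data. The downside is that the question about long-stay patients is then answered only indirectly, through factors known at randomisation. Any subgroup contrast in a trial of this size will also remain imprecise.
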